### Sample size calculation

Two different sample sizes were calculated: one for the estimation of *P.vivax* failure rate for chloroquine (28-day follow-up) and for Primaquine (2-year follow-up) in a cohort of *P.vivax* patients initially treated with the current radical cure regimen, and the second for the population survey on *P.vivax* prevalence (in a random sample of the study population).

- ***P.vivax population survey***

A total2,100 individuals at risk of malaria were estimated in the 4 study communes (census February 2009). According to the provincial malaria station (PMS) data on surveys carried out in April-May, the overall parasite rate was around 16% (ranging from 5 to 39% across hamlets) and the prevalence of *P.vivax* at 9%. In order to detect a minimal prevalence of 9% with 3% precision and at 5% significance level, a total of 300 individuals is needed for the survey (“CSample” command/EpiInfo6). After “finite population correction” and adding 10% security margin, a final sample size of 300 individuals would be sufficient. Since there are a total of about 370 households and in order to simplify sampling procedures, one individual in each house visited for the screening will be randomly selected to participate in the survey. This will be done by randomly choosing from the census file. The selected individual will be asked oral informed consent before starting in-depth interview.

- ***P.vivax cohort***

Between 2003 and 2007, *P. vivax* late parasitological failure to CQ was monitored in several Central Vietnam provinces and ranged from 0% to 5.7% (13). Therefore, to detect a failure rate as low as 5% with a 3% precision at 5% significance level, a minimum of 185 individuals are needed (“CSample” command/EpiInfo6). Assuming a maximum drop out rate of 10% during the first 28 days, a total of 204 cases will be necessary. For the estimation of a similar PQ failure rate after 2 years of follow-up, a total of 230 patients should be included with a maximum of 20% drop out during the 2-year follow-up.

By including 250 vivax patients in the cohort, and assuming a maximum drop out rate of 20% during the 2-year follow-up, we can expect to get a final database of 200 patients with a complete follow-up (i.e. 31 successive sampling results) for the modelling of *P.vivax* new infections/relapses.

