## Specific objectives

1. To establish in a defined cohort of *P.vivax* patients, the short and long term efficacy of the new national treatment guideline in preventing recrudescences and relapses;
2. To characterize *P.vivax* transmission dynamics and indentify vulnerable groups among the local population (in a representative sample of the study population);
3. To set up a new tool, based on genotyping, serology and modelling able to accurately distinguish between *P.vivax* new infections and relapses.

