More detailed information on the socio-economic status, preventive measures employed and known malaria risk factors will be collected in one family member randomly chosen by drawing a folded paper containing a number (one number per household dwellers). The chosen number will correspond to the individual code number of the person to be included in the survey. If the chosen individual is absent or refuses to take part, he/she will not be replaced by another household member, the survey procedures will not be done in that household. Every effort will be made to trace an absent survey participant (survey team returning at different times during the whole duration of the survey in that village). After informed consent, the survey participant will undergo a detailed interview on his last months’ activities in relation to malaria exposure, and to preventive measures taken. In addition to the blood slide, one more blood sample will be taken for haemoglobin measurement (Hemocue) and another one on filter paper for later serology and genotyping. Microscopic examination will done on the spot and if a patient is detected with a *P.vivax* mono-infection, he will be invited to enter the cohort following similar procedures as during the screening (selection criteria and informed consent). Non eligible *P.vivax* patients, and other survey participants (with malaria or other diseases) will be treated according to the national guidelines.

All data will be recorded onto a pre-coded standardised questionnaire (Annex2).

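### The survey size of 300 already contains the finite population correction but not the stated 10% margin; with the margin it is about 330, and one-per-household sampling calls for household-size weights

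*Protocol*

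**What the plan says.** The Protocol's section on sample size calculation sets the survey size. The population is given as "A total2,100 individuals at risk of malaria were estimated". The target is worded "In order to detect a minimal prevalence of 9% with 3% precision and at 5% significance level", and for this "a total of 300 individuals is needed for the survey". The next sentence applies a finite population correction and a margin and concludes, "adding 10% security margin, a final sample size of 300 individuals would be sufficient".

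The same paragraph then sets the sampling procedure. There are about 370 households and, to simplify sampling, "one individual in each house visited for the screening will be randomly selected to participate in the survey". This paragraph says the choice is made at random from the census file. The section on screening and survey describes it as "one family member randomly chosen by drawing a folded paper containing a number", adds that the number drawn corresponds to the person's individual code, and allows no replacement in the household if that person is absent or refuses. It also requires repeated attempts to trace absentees.

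The survey serves the second specific objective, which is to be met "in a representative sample of the study population".

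**The concern.** A finite population correction lowers a sample size and a security margin raises it. Both are said to have been applied to 300, and the result is again 300. Either the first 300 is not the uncorrected number, or one step was not carried out. If the margin is missing, a sample of exactly 300 has no reserve, and any loss takes the precision below the stated 3 points.

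The second matter is the fit between formula and design. The formula is the one for a simple random sample of individuals. Under the procedure a resident of a two-person house is selected with probability 1/2 and a resident of a ten-person house with probability 1/10. The unweighted mean over respondents then estimates an average over households, not over residents. The survey samples supply CSP seroprevalence, PCR prevalence of sub-patent infection, genetic diversity and risk factors. Several of these feed the model for the probability that an episode is a new infection.

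**Working it through.** Inputs, all from the Protocol's sample size section: p = 0.09, d = 0.03, 5% significance level read as a two-sided 95% interval (z = 1.96), N = 2,100, about 370 households.

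**Reproducing the stated 300**

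1. Uncorrected: n0 = z² p(1 − p)/d² = 1.96² × 0.09 × 0.91/0.03² = 349.6, i.e. 350.
2. Corrected: n = n0/(1 + n0/N) = 349.6/(1 + 349.6/2,100) = 299.7, i.e. 300.
3. With the 10% margin: 299.7 × 1.1 = 329.7, i.e. 330. Dividing instead gives 299.7/0.9 = 333.0; starting from the rounded 300, 300/0.9 = 333.3, i.e. 334.
4. Margin first, correction second: 325 (× 1.1) or 328 (/0.9).

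The first 300 matches step 2 and not step 1, so it already contains the correction. None of the orders in steps 3 and 4 returns 300.

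**Cross-check with the cohort calculation in the same section.** For 5% ± 3%: 1.96² × 0.05 × 0.95/0.03² = 202.7 uncorrected, and 202.7/(1 + 202.7/2,100) = 184.9 corrected. The stated 185, from the same software command, also matches the corrected value. There the 10% is then added: 185 × 1.1 = 203.5, given as 204. The same convention applied to the survey gives 330.

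**What the missing margin costs.** Half-width = 1.96 × √[p(1 − p)/n × (1 − n/N)].

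| Respondents | Half-width (points) |
|---|---|
| 270 (300 less 10%) | 3.19 |
| 300 | 3.00 |
| 330 | 2.83 |
| 333 (370 less 10%) | 2.82 |
| 370 | 2.65 |

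**What the procedure delivers.** About 370 people are selected, more than 330 or 334. The non-response that still leaves 300 is 1 − 300/370 = 18.9%.

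**Unequal selection.** Mean household size is 2,100/370 = 5.7. The distribution of sizes is not given, so what follows rests on assumption.

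- *Precision.* The Kish approximation for the weighting effect is 1 + CV², with CV the coefficient of variation of household size. For an assumed CV of 0.3 to 0.5 it is 1.09 to 1.25. The weighted half-width is then 2.94 to 3.15 points with 333 respondents and 2.76 to 2.96 with 370.
- *Bias if unweighted.* It is zero if prevalence does not vary with household size. Suppose half the households have 3 members and half 8.35 (mean 5.7). With prevalences of 6% and 12%, the population value is (3 × 6 + 8.35 × 12)/11.35 = 10.4%, the unweighted value is 9.0%, and the bias is −1.4 points. With 12% and 7%, the population value is 8.3%, the unweighted value is 9.5%, and the bias is +1.2 points. These scenarios show only that the sign is open.

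**The case against.** The strongest reply is that the error sits in the justification and changes no sampling step. The paragraph goes on to select one person in each of about 370 households, which exceeds the corrected figure. This stands. A reader might infer that the survey is too small; the documents do not support that, since 300 respondents are reached at 81% response and absentees are to be traced repeatedly.

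A reader might also infer that the finite population correction was applied twice. Correcting 300 again gives 300/(1 + 300/2,100) = 262.5, then 289 (× 1.1) or 292 (/0.9), which could have been rounded up to 300. Redundant wording with the margin left out fits equally well, and the text does not decide between them.

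A third inference would be that the prevalence estimate is biased. That needs prevalence to depend on household size and an unweighted analysis, and the Protocol states neither. Weighting may be set out in an analysis plan that is not at hand. One person per house also removes clustering within households. Moreover, the whole population is invited to microscopy screening, so slide prevalence does not rest on the survey alone; this does not cover serology or the interview data.

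Finally, the census-file and folded-paper descriptions might be read as two different samples. Both give each household member the same chance, and the numbers drawn are individual codes assigned at the census. It is a wording conflict.

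**Conclusion.** The size statement is wrong as written. The 300 is the corrected number, the 10% margin is not in it, and the sequence should be 350, 300, about 330 (333 to 334 by division). This rests only on the Protocol's inputs and z = 1.96, and the cohort calculation in the same section supports it. The consequence on paper is a half-width of about 3.2 points instead of 3 if 10% of 300 are lost. In the field, about 370 selections cover the gap.

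Selection probability equal to 1/household size is a fact of the design, and weighting is the direct way to serve the representativeness that the second objective asks for. The size and direction of any unweighted bias cannot be determined from the documents, and the loss of precision can only be bracketed by assumption. Severity is minor: the point concerns the survey and leaves the cohort's primary endpoints untouched.

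**What to change.** Restate the survey size as about 350 uncorrected, 300 after correction for 2,100 residents, and about 330 with the 10% margin. Add that one person in each of about 370 households will be approached without replacement, which covers this number and leaves 300 respondents at up to about 19% non-response.

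State, in the Protocol or the analysis plan, that survey estimates (prevalence, CSP seroprevalence, risk factors) are weighted by census household size, with design-based standard errors.

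Use one description of the selection within households in both sections, or say how the census-file and folded-paper steps fit together.

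The cost is a few sentences and a survey-weight statement in the planned STATA analysis. Household membership is already in the census, so no new data are needed. The downside is slightly wider intervals.

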# MATERIALS & METHODS

## Study site and population

The study will be carried out in the 2 neighbouring communes of Tra Leng and Tra Don situated in Nam Tra My district, Quang Nam Province, Central Vietnam, where several malaria outbreaks have occurred in the past, and currently with most *P.vivax* casesin the province (11). The latter come mostly from Villages 1, 2 and 3 in Tra leng and from Village 3 in Tra Don commune. The commune health centre (CHC) of Tra leng is situated in Village 1, which is contiguous to Village 3, while Village 2 is situated at 2h walking distance through the forest on the top of a mountain. Village 4 is located even further (4h walking distance) and will be included in the study area in a second phase (March 2010) in order to increase the recruitment rate. The area is still densely forested and mountainous, a perfect site for *Anopheles dirus*, though the main vector species identified in entomological collections by the Provincial Malaria Station (PMS) is *An.minimus A,* together with other species such as *An.vagus, An.aconitus,* or *An.philippinensis* (12).

The climate is sub-humid with an average annual rainfall of about 1,200-2,000mm and two seasons: the dry season from December to April, and rainy season from May to November. Malaria transmission is perennial with 2 peaks: the first at the beginning of the rain (March-May), and the second between August and October. Annual reports from the national program show that about 40 to 45% of the malaria cases are due to *P.vivax* and all age groups are infected. The 2 communes totalled up to 400 and 300 cases, respectively in 2005 and 2006, with a total annual incidence of about 150 *P.vivax* cases/1000 populations. In 2007, the incidence dropped to 153 cases, and in 2008 only 106 cases were detected. Despite the decreasing incidence, more cases can probably be found by systematic screening.

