## Blood samples processing

Blood slides will be examined directly, either in the field during the screening/survey or at Tra leng CHC during PCD and cohort follow-up. Thick and thin blood smears will be stained with Giemsa 4% for 45 minutes and examined for species diagnosis and parasite density. The later will be determined by counting the number of asexual parasites for 200 white blood cells (WBC) and assuming 8,000 WBC/µl. Slide reading will be blinded to the patient’s details and symptoms, first by the CHC microscopist, and systematically double checked by the senior microscopist from NIMPE. Discrepant results will be re-read by the 2 microscopists together. Quality control will be carried out, every 3 months, on all positive and 10% of negative slides at NIMPE, Hanoi.

Filter papers, after complete drying (outside direct sun light), will be kept in individual plastic bags, stored within a bigger bag containing silica gel (to avoid direct contact of blood with silicagel) and kept at 4°C (fridge) at Tra Leng CHC. CSP-ELISA and genotyping (by micro-satellites) will be carried at ITM Antwerp (Lab. Dept of Parasitology) by the Msc student from NIMPE, Hanoi during her 2nd year of training, and after Msc graduation and transfer of techniques, at NIMPE, Hanoi.

- CSP-ELISA will be carried out on all survey samples to estimate the transmission intensity (anti-CSP antibodies prevalence), and on samples collected during 28-day and monthly follow up visits, to follow the evolution of anti-CSP Ab and identify possible new *P.vivax* infections. This technique is currently optimized and standardised by a Belgium PhD student, at ITM Antwerp.
- Species specific PCR will be performed on all blood samples collected on filter paper in order to confirm the *P.vivax* mono-infection (cohort patients), the overall species distribution and the prevalence of sub-patent malaria infections (survey samples). This will be done by using SnM-PCR15 (semi-nested multiplex PCR) to amplify ssrDNA sequences of Plasmodium species. Only samples with a *P. vivax* mono-infection at inclusion will be used for the analysis of the cohort patients.

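### The cohort minimum of 185 does not follow from its stated inputs (they give 203), and the 3% precision is not supported for the 2-year recurrence endpoint

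*Protocol*

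**What the plan says.** All the cohort figures are in the protocol's section on sample size calculation.

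- **Source of the rate.** In earlier monitoring, "late parasitological failure to CQ was monitored in several Central Vietnam provinces and ranged from 0% to 5.7" per cent. From this the protocol takes 5%.
- **Day-28 size.** The protocol states that, "to detect a failure rate as low as 5% with a 3% precision at 5% significance level, a minimum of 185 individuals are needed", a figure obtained with an EpiInfo6 command. It is then raised for losses: "Assuming a maximum drop out rate of 10% during the first 28 days, a total of 204 cases will be necessary".
- **2-year size.** "For the estimation of a similar PQ failure rate after 2 years of follow-up, a total of 230 patients should be included", with at most 20% drop-out.
- **Planned cohort.** 250 patients, of whom 200 are expected to complete 2 years.

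A finite-population correction is named in the same section, but only for the prevalence survey, whose population is described thus: "A total2,100 individuals at risk of malaria were estimated in the 4 study communes (census February 2009").

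The section on study endpoints defines two primary endpoints: treatment failure at day 28, and the incidence of recurrent *P. vivax* infection after day 28 over the 2 years. The section on blood samples processing adds that only samples with a PCR-confirmed *P. vivax* "mono-infection at inclusion will be used for the analysis of the cohort patients".

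**The concern.** There are two separate problems.

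First, a reader who puts 5%, 3 points and 95% confidence into the usual single-proportion formula does not get 185. If a correction for the number of residents has been applied, it is out of place. It shrinks a sample drawn at random from a finite population whose own proportion is the target. The cohort consists of infected, treated patients, and their failure rate is meant to inform a national treatment guideline, not to describe 2,100 villagers.

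Second, the 2-year figure is sized on a different quantity from the endpoint. A chloroquine parasitological failure rate is carried over to primaquine with no primaquine or relapse data. The endpoint also counts any recurrence, so it includes new infections in an area where the protocol describes transmission as perennial. If the true 2-year proportion is above 5%, the long-term result will be less precise than the protocol says.

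**Working it through.** **Inputs from the protocol:** p = 5%; precision d = 3 points; 5% significance (two-sided assumed, z = 1.96; sidedness is not stated); 2,100 residents; 10% loss to day 28; 20% loss to 2 years; 250 enrolled.

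**Reproducing 185**

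- Plain formula: n = z²p(1−p)/d² = 1.96² × 0.05 × 0.95 / 0.03² = 202.7, so 203. This is not 185. A one-sided z gives 143, which is not 185 either.
- With a finite-population correction: 202.7 / (1 + 202.7/2,100) = 184.9, so 185. A population of 2,000 gives 184.1, which also rounds up to 185; 5,000 gives 194.8.
- The survey figure follows the same pattern. For 9% with 3 points, 1.96² × 0.09 × 0.91 / 0.03² = 349.6; corrected to 2,100 it is 299.7, and the protocol states 300.

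**Allowance for losses**

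- 185 × 1.10 = 203.5, the stated 204; dividing gives 185/0.9 = 205.6, so 206.
- 185/0.8 = 231.25, so 232, against the stated 230 (230 × 0.8 = 184, one below the minimum).
- From 203, using n/(1−loss): 203/0.9 = 225.6, so 226; 203/0.8 = 253.8, so 254.

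**Precision from the planned 250 at day 28** (half-width = 1.96 × √(p(1−p)/n))

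- 250 × 0.9 = 225 evaluable. At 5%: 1.96 × √(0.0475/225) = 2.85 points, inside 3.
- At 5.7%, the top of the cited range: 3.03 points.
- A sample of 185 would itself give 3.14 points at 5%.
- PCR exclusions have no stated allowance. The 225 could lose 22 patients (22/225 = 9.8%) and still leave 203.

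**Precision from the planned 250 at 2 years**

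250 × 0.8 = 200 completers. The protocol gives no expected recurrence, so every row except 5% is an assumption. Treating the endpoint as the proportion with at least one recurrence is a simplification.

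| 2-year proportion | Half-width, n = 200 | Evaluable n for 3 points |
|---|---|---|
| 5% (protocol's rate) | 3.0 points (3.02) | 203 |
| 10% (assumed) | 4.2 points | 385 |
| 20% (assumed) | 5.5 points | 683 |
| 30% (assumed) | 6.4 points | 897 |

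**The case against.** **The cohort is 250, not 185.** This is the strongest reply, and for day 28 it stands. A reader might infer from the wrong minimum that the stated precision is missed for both primary endpoints. The documents do not support that: 250 exceeds the corrected requirement of 226, and 225 patients give 2.85 points at 5%. The 200 completers belong to the 2-year follow-up and should not be used for day 28. PCR exclusions could erode the margin, but the protocol gives no rate for them, so no shortfall is shown.

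**The correction is never stated for the cohort.** True. It is inferred from an exact match with 2,100 and from the same pattern in the survey figure. Whatever produced 185, the stated inputs do not.

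**The 5% may be meant for relapse only.** The protocol plans genotyping, serology and modelling to separate relapses from new infections, so a low primaquine failure rate is a readable target. But the primary endpoint as written is recurrent infection of any origin, and no source for 5% is given even for relapse alone.

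**The site's incidence seems to show how far the precision falls short.** The study site section reports "with a total annual incidence of about 150" *P. vivax* cases per 1,000, and a reader might infer a recurrence well above 5% and a definite widening of the interval. The figures do not allow it. That rate is tied to 2005–2006, and the section then reports a fall to 153 cases in 2007 and 106 in 2008. The denominator of the 106 is not stated, nor clearly whether all are *P. vivax*. By the protocol's own account, available techniques cannot separate relapses from new infections, so adding a relapse rate to these counts would count relapses twice. They also describe residents in general, not treated patients sampled every month.

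**Conclusion.** The point holds in two parts of unequal weight.

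- **Minimum size.** The stated 185 is wrong for its inputs; it should be 203. The effect is small, because the planned 250 still meets 3 points at day 28 if the failure rate is 5%, loss is 10% and PCR exclusions stay below about 10% of those remaining. The differences of 204 from 206 and 230 from 232 are minor.
- **2-year endpoint.** The 3% precision is not supported, because the 5% comes from another drug and another event than the endpoint. Even at exactly 5%, 200 completers give 3.02 points, a negligible excess. How much wider the interval becomes depends on a recurrence proportion that the protocol does not give, so the table shows a range of assumptions and not a predicted shortfall.

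**What to change.** Keep the enrolment target of 250 and restate the reasoning in the sample size section:

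1. Give the cohort minimum as 203 evaluable patients, with no finite-population correction, and 226 and 254 enrolled after 10% and 20% loss, using n/(1−loss). Say openly that 250 is four below 254 and gives 3.02 points at 5% with 200 completers.
2. State the day-28 precision expected from 250 as about ±2.85 points at 5% before PCR exclusions, and add an assumed allowance for those exclusions.
3. For the 2-year endpoint, replace the reference to a comparable primaquine failure rate with the expected recurrence as a labelled assumed range, and give the precision with 200 completers: ±3.0 points at 5%, 4.2 at 10%, 5.5 at 20% and 6.4 at 30%.

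The cost is wording only. The stated 2-year precision becomes less favourable, but no patients, visits or procedures are added.
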